#### Specific

To determine whether pharmacological intervention with a low-dose combination of spironolactone (25 mg/day), pioglitazone (3.75 mg/day), and metformin (425 mg/day) within a single tablet (mini-spiomet) over 1 year in “mismatch” girls with early puberty, reduces hepatic and visceral fat significantly more than placebo, as assessed by MRI.To ascertain whether in girls treated with mini-spiomet, the reduction of hepatic and visceral fat associates to (1) a greater deceleration of bone maturation [as evaluated by Δ bone age (BA)/Δ chronological age (CA) ratio over 1 year]; (2) a slower pubertal *tempo* (as judged by the progression of Tanner stage); and (3) more normal levels of insulin, IGF-I, inflammation markers, sex steroids, HMW-adip, CXCL14, and GDF15, as compared to girls who received placebo.To assess whether the benefits of mini-spiomet on hepato-visceral fat and endocrine-metabolic markers on-treatment are still detectable 1 year after treatment discontinuation.To evaluate the tolerance and safety of mini-spiomet over 1 year (by assessing safety parameters), as well as the acceptance of the tablet (through a specific visual questionnaire).

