#### Secondary outcomes

◦ Clinical variables: weight, height, BMI, waist and hip circumference and their ratio (WHR), systolic blood pressure (SBP), diastolic blood pressure (DBP), and Tanner stage [4].◦ Endocrine-metabolic variables:fasting glucose, insulin, HOMA-IR [5], IGF-ILH, FSH, testosterone, androstenedione, SHBG, FAI and estradioltriglycerides; total, low- and high-density lipoprotein (LDL and HDL) cholesterolultra-sensitive C-reactive protein (usCRP), GDF-15, HMW-adip, CXCL14.◦ Safety markers: blood count, circulating concentrations of alanine transaminase (ALT), aspartate transaminase (AST), gammaglutamyltransferase (GGT), thyroid-stimulating hormone (TSH), urea, creatinine, electrolyte panel, vitamin B12, folic acid.◦ Abdominal fat partitioning (subcutaneous visceral area) and intrahepatic fat by MRI.◦ Dietary habits, tablet acceptability, study adherence, adverse events.

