### Sample size {14}

In a previous study performed in girls with a history of low-BW and rapid postnatal catch-up in weight, metformin treatment for 4 years (425 mg for 2 years, then 850 mg for 2 years) slowed down the accelerated bone maturation [38]. The progression of bone maturation, as assessed by the mean ratio of Δ BA over Δ CA, was faster in untreated girls [≈1.20 ± 0.2 (SD)] as compared to metformin-treated girls [≈1.00 ± 0.2 (SD)] (*P*≤0.05). To obtain a significance level of 0.05% and power of 90%, a total of 42 girls (21 in each study arm) must be included to detect the minimal relevant difference in bone age progression (1.20 vs 1.00 years) (https://clincalc.com/stats/samplesize.aspx). The number of patients has been further increased (*n*=32 in each study arm) to guarantee the necessary sample size, in the case up to one third of the participants drop out of the study.

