The clinical laboratory at both HJT and HSJD will be responsible for analyzing (1) glucose (by the glucose oxidase method); (2) fasting insulin, IGF-I, SHBG, and usCRP (by immuno-chemiluminescence); (3) LH, FSH, and oestradiol (by immuno-chemiluminescence); (4) total cholesterol, LDL-cholesterol, HDL-cholesterol, and triglycerides (by molecular absorption spectrometry).Circulating testosterone and androstenedione concentrations will be centrally assessed at the Bioanalysis Research lab [Institut Hospital del Mar d'Investigacions Mèdiques (IMIM), Hospital del Mar] by liquid chromatography-tandem mass spectrometry. The free androgen index (FAI) will be calculated with the following formula: testosterone (nmol/L) × 100/SHBG (nmol/L).The analysis of circulating HMW-adip, GDF-15, and CXCL14 concentrations will be centralized at the Metabolic Endocrinology laboratory (IRSJD). Circulating levels of HMW-adip will be analyzed by ELISA (Millipore, St Louis, MO), with intra- and inter-assay coefficients of variation (CVs) <9%. Serum GDF-15 will be assessed using a specific human ELISA kit (R&D Systems, Minneapolis) with intra- and inter-assay CVs <6%. Serum CXCL14 will be assessed using a specific ELISA kit (Ray Biotech, Norcross, GA, USA), with a sensitivity of 0.7 ng/ ml, and inter- and intra- assay CV less than 12%.

*Safety markers analysis:* The clinical laboratories at HJT and HSJD will analyze (1) blood count (by flow cytometry and colorimetric assay); (2) circulating levels of ALT, AST, GGT, TSH, urea, electrolyte panel, and creatinine (by molecular absorption spectrometry); and (3) vitamin B12 and folic acid (by immuno-chemiluminescence).

*Abdominal and hepatic fat assessment:* Abdominal fat distribution *(subcutaneous and visceral)* and intrahepatic fat will be analyzed by MRI at both clinical sites with the same scan [multiple slice 1.5 Tesla scan (Signa LX Echo Speed Plus Excite, General Electric Healthcare, Milwaukee, WI)]. The assessments will be performed at Clínica Girona (Girona) and CETIR Medical Centre (Barcelona). Scans will be performed by the same operator at each center, blinded to the treatment allocation, at times 0, 6 months, 1 year, and 2 years. A central reader blinded to treatment allocation will be appointed to process and interpret the images from both study centers (QUIBIM, Valencia, Spain).

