*Dietary habits:* The quality of the dietary habits will be assessed by a modified version of the Kidmed questionnaire. Girls will complete the test during the clinical visits at the corresponding center (at times 0, 6 months, 1 year and 2 years).

*Acceptability of the tablet:* The patient's opinion regarding the palatability and swallowability of the tablet will be recorded by using a simple questionnaire with numerical rating scales and the integrated 100 mm visual analog scale (VAS)/facial hedonic scale [3, 4]. Patients will answer the questionnaire during the clinical visits at each center at times 6 months and 1 year.

All outcomes will be measured as previously described (domain, specific measure, and time points), stated as mean values, and compared between groups at the specific time points.

Figure 2 depicts the schedule of enrolment, interventions, and assessments.

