## Statistical methods

### Statistical methods for primary and secondary outcomes {20a}

The statistical analyses will be performed with the SPSS program, version 23.0 (SPSS, Chicago, Illinois, USA). The analysis of quantitative variables of independent groups will be performed using ANOVA for repeated measurements in models adjusted for potential confounding variables. The association between BA, clinical variables, endocrine-metabolic, and imaging variables will be sought by correlation and multiple regression analysis. A statistical analysis will be done by intention to treat and another with the patients who have completed follow-up. *p*<0.05 will be considered statistically significant.

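### The plan does not tie the 1-year fat objective to a month-12 contrast adjusted for baseline, although baseline fat is scheduled for every girl

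*Protocol article*

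**What the plan says.** Four places in the protocol article bear on how the fat result will be obtained.

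- **Objectives, Specific.** The first objective is whether one year of mini-spiomet "reduces hepatic and visceral fat significantly more than placebo, as assessed by MRI". A later objective asks whether the benefits "are still detectable 1 year after treatment discontinuation".
- **Secondary outcomes.** Fat appears as "Abdominal fat partitioning (subcutaneous visceral area) and intrahepatic fat by MRI", with no metric and no time point.
- **Assessment of outcomes.** MRI is performed "blinded to the treatment allocation, at times 0, 6 months, 1 year, and 2 years". The section closes with a general sentence that all outcomes will be "stated as mean values, and compared between groups at the specific time points".
- **Statistical methods for primary and secondary outcomes.** Quantitative variables are to be analysed by "ANOVA for repeated measurements in models adjusted for potential confounding variables". The section does not name the visits that enter, the model term that is tested or the adjustment variables.

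For bone age the article does fix a baseline-referenced measure, the ratio of bone-age increase to chronological-age increase. It fixes none for fat or the laboratory markers.

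**The concern.** The objective concerns a reduction, which calls for a baseline reference. The assessment section describes a comparison of means at each visit and does not mention baseline. The statistical section describes a repeated-measures model and does not say which of its terms answers the objective.

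An analyst could therefore report a plain month-12 comparison of levels, an arm main effect over visits, an arm-by-time test or a baseline-adjusted month-12 difference, and claim support in the text for each. These differ in their chance of detecting a real effect and in their sensitivity to a chance imbalance at baseline. Reduction of ectopic fat is the mechanism that the trial proposes, so the answer matters even though fat is a secondary outcome. The same wording governs insulin, HMW-adiponectin, SHBG and the other continuous markers.

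**Working it through.** **The plan's own figure.** The only sample-size calculation is for bone age: difference 0.20, SD 0.2, power 90%. With two-sided alpha of 5% (the text prints 0.05%), n per arm = 2 × [(1.960 + 1.282) × 0.2/0.2]² = 21.0. This reproduces the stated 21 per arm, and 21/(1 − 1/3) = 31.5, rounded up to 32. It says nothing about fat, for which the documents give no effect, SD or correlation.

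**Inputs for fat (all assumed unless noted).**
- n = 26 per arm at month 12. This lies between the 21 and 32 in the sample-size section.
- True effects of 0, 0.36, 0.6 and 0.3 SD at months 0, 6, 12 and 24.
- Equal correlation ρ between any two visits, from 0.3 to 0.8.
- Two-sided 5% tests. The plan gives 0.05 without sidedness.

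**Month-12 contrasts.** In units of the fat variance, the per-girl variance v is:
- plain level: 1
- change from baseline: 2(1 − ρ)
- ANCOVA on baseline: 1 − ρ²

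The noncentrality is 0.6/√(2v/26). At ρ = 0.7:
- level: 0.6/√(2 × 1/26) = 0.6/0.277 = 2.16, power 0.56
- change: v = 0.60, 0.6/0.215 = 2.79, power 0.78
- ANCOVA: v = 0.51, 0.6/0.198 = 3.03, power 0.84

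**Repeated-measures terms, if all four visits enter.** At ρ = 0.7:
- Arm main effect: it estimates (0 + 0.36 + 0.6 + 0.3)/4 = 0.315 SD. Its variance factor is (1 + 3ρ)/4 = 0.775, so the noncentrality is 0.315/√(2 × 0.775/26) = 1.29 and power is 0.24.
- Arm-by-time, 3 df: the squared deviations of the effects from 0.315 sum to 0.1827. Then λ = (26/2) × 0.1827/(1 − 0.7) = 7.92 and power is 0.64.

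| ρ | plain level | change | ANCOVA | arm main effect | arm-by-time, 3 df |
|---|---|---|---|---|---|
| 0.3 | 0.56 | 0.43 | 0.60 | 0.37 | 0.30 |
| 0.5 | 0.56 | 0.56 | 0.69 | 0.29 | 0.41 |
| 0.7 | 0.56 | 0.78 | 0.84 | 0.24 | 0.64 |
| 0.8 | 0.56 | 0.92 | 0.94 | 0.23 | 0.83 |

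The plain level does not gain as ρ rises, because it uses no baseline. The arm-by-time test does gain, because it uses baseline. It does not, however, itself estimate the month-12 difference.

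**Sensitivity.** At 32 per arm and ρ = 0.7, level and ANCOVA have power 0.66 and 0.91. At 21 per arm they have 0.48 and 0.76. If only months 0, 6 and 12 enter, arm-by-time has 2 df and power 0.70 at 26 per arm.

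**Chance imbalance.** The standard error of the baseline difference is √(2/26) = 0.277 SD. A baseline difference beyond 0.3 SD in either direction therefore arises in about 28% of trials. A plain level comparison carries ρ times that difference forward. At ρ = 0.7 this is 0.7 × 0.3 = 0.21 SD, against an assumed effect of 0.6 SD. ANCOVA removes it.

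**The case against.** The strongest reply is that the sentences can be reconciled. The sentence on means sits in the data-collection section and gives only an aggregation and time points. It never says that the comparison is unadjusted. The model is given in the statistical section, and a repeated-measures model with arm contrasts at each visit would satisfy both. Baseline might be among the unnamed confounders, and such detail is often left to a fuller protocol or SAP. This stands as far as it goes: the text permits the better analysis. It does not select it, and the sentence on means, taken at face value, points to a plain comparison.

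Several stronger readings are tempting and are not supported.

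- *The article sets three conflicting fat endpoints.* Allocation is randomised 1:1, so the expected baseline difference is zero. The month-12 level, change and ANCOVA contrasts then target the same effect. They differ in precision and in exposure to chance imbalance.
- *Most of the described approaches throw baseline away.* Only the plain level comparison does. The change score and the arm-by-time test use it.
- *The deciding test is a four-visit main effect.* The statistical section names neither visits nor term. The trial design separates on-treatment from post-treatment effects, persistence has its own objective, and the blinding section locks an on-treatment database before the statisticians are unblinded. The interim-analysis section does place analysis after the trial has finished, so timing is not fully clear, but nothing puts the off-treatment visit into the on-treatment test.
- *Fat is a key secondary endpoint.* The article gives it no such rank. It is the first specific objective and one of many secondary outcomes.

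The objection that the power figures rest on undocumented inputs also stands. At ρ = 0.3 the loss is small, and the missing-data section fills gaps from earlier visits, so the intention-to-treat number would be 32 per arm.

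**Conclusion.** The point holds as a gap in specification with a cheap and better alternative. The article does not state that the 1-year fat objective is tested as a month-12 contrast adjusted for baseline, and its general sentence on outcomes describes a comparison that, done plainly, ignores baseline.

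The cost of a plain level comparison relative to ANCOVA ranges from about 4 points of power at ρ = 0.3 (0.56 against 0.60) to about 38 points at ρ = 0.8 (0.56 against 0.94). These figures assume 26 per arm and a 0.6 SD effect. The loss from an arm main effect is larger, but arises only if that term is the test and baseline and the off-treatment visit both enter as visits. The choice of ANCOVA does not depend on the unknown correlation: in every row of the table it has the highest power. The primary bone-age outcome is not affected.

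**What to change.** Replace the general sentence at the end of the outcome-assessment section and align the statistical section with it. Suggested content:

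*For hepatic fat, visceral fat and each continuous secondary variable, the on-treatment result is the difference between arms at month 12, estimated with the baseline value of that variable as covariate (ANCOVA, or a mixed model with baseline, visit and arm-by-visit terms). Month 6 and month 24 are reported as separate contrasts, and month 24 answers the objective on persistence after treatment.*

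The cost is two sentences and one covariate per model. Baseline MRI and blood sampling are already scheduled for every girl, so no data or visits are added. The change should be made before the on-treatment database is locked, because the statisticians are unblinded at that point.

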### Criteria for discontinuing or modifying allocated interventions {11b}

In all participating girls, safety markers [blood count, circulating levels of alanine transaminase (ALT), aspartate transaminase (AST), gammaglutamyltransferase (GGT), thyroid-stimulating hormone (TSH), urea, creatinine, electrolyte panel, vitamin B12, folic acid] will be assessed at treatment start, after 6 months and 1 year on treatment, and after 1 year off treatment, as well as upon reporting any adverse events. Glucose blood levels <65 mg/dL and a progressive increase of creatinine, urea, transaminase or potassium levels, will be a reason for discontinuing the medication. In addition, the existence of signs and/or symptoms of hypoglycemia, the appearance of a persistent skin rash, abdominal pain, persistent nausea and/or vomiting, headaches, sinusitis, and severe bacterial infections, will be also a reason for discontinuation. In those cases, hepatic and renal function will be periodically monitored until the disappearance of the symptoms or the normalization of the altered parameters.

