### Procedure for unblinding if needed {17b}

If a girl/family wishes to withdraw from the trial or if an adverse event leads to withdrawal from the study, then the family will be invited to an end-of-study visit which will be followed by disclosure of treatment allocation. The girl will continue to receive standard care.

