### Methods in analysis to handle protocol non-adherence and any statistical methods to handle missing data {20c}

An intention-to-treat analysis will be performed including all participants randomized to either placebo or mini-spiomet, ignoring non-compliance, protocol deviations, withdrawal, and anything that happened after randomization. If necessary, for the withdrawn participants, the missing data will be filled with the data of previous visits.

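### Laboratory safety markers fall under the general rule of arm means at fixed visits, with carry-forward, which does not show how many girls met a laboratory stopping criterion

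*Protocol article*

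**What the plan says.** Safety is a specific objective of the trial: "To evaluate the tolerance and safety of mini-spiomet over 1 year (by assessing safety parameters", as the Specific objectives put it. The Secondary outcomes section makes the laboratory markers an outcome. The entry begins "Safety markers: blood count, circulating concentrations of alanine transaminase (ALT" and goes on to other liver, thyroid, renal, electrolyte and vitamin measures. Fasting glucose is listed separately, among the endocrine-metabolic variables.

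The section Assessment of outcomes ends with one sentence for all outcomes: they will be "stated as mean values, and compared between groups at the specific time points". Section {20a} sends quantitative variables to repeated-measures ANOVA, which also compares means, and adds: "A statistical analysis will be done by intention to treat and another with the patients who have completed follow-up". Section {20c} says that, if necessary, "for the withdrawn participants, the missing data will be filled with the data of previous visits".

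Section {11b} takes the safety markers at start, 6 months, 1 year and 1 year off treatment, "as well as upon reporting any adverse events". It also sets the laboratory reasons for stopping medication: glucose below 65 mg/dL, or a progressive increase of creatinine, urea, transaminase or potassium. Under {17b}, if a family withdraws or an adverse event leads to withdrawal, "then the family will be invited to an end-of-study visit which will be followed by disclosure of treatment allocation".

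**The concern.** The laboratory markers are numeric outcomes, and no sentence takes them out of the general rule. Read as written, laboratory safety is compared between arms through means at the scheduled visits.

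That does not match how the protocol defines laboratory harm. The {11b} criteria are met or not met by one girl at a time. Two similar arm means are compatible with no girl or with three girls per arm having met a criterion.

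The carry-forward rule adds a smaller problem. A girl who withdraws after an abnormal result can appear in the 1-year mean with a value from before the abnormality. The unscheduled sample that showed it has no stated place in the summary. At stake is the between-arm laboratory evidence for a stated safety objective in girls aged 8.0 to 9.5 years.

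**Working it through.** **Inputs from the protocol.** 32 girls per arm (Trial design; {16a}: 16 + 16 per arm over two centers). Significance level 0.05: {14} prints 0.05%, but 0.05 is the level that reproduces its sample size. I assume two-sided tests.

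**The plan's own figure.** With a difference of 0.20, SD 0.2 and power 90%, n per arm = 2 × (1.960 + 1.282)² × (0.2/0.2)² = 21.01, which matches the stated 21. Allowing for one third dropping out, 21/(1 − 1/3) = 31.5, so 32. This sizes the trial for bone age. Nothing is sized for laboratory safety.

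**What a mean can show when a few girls are extreme.** Let m of n girls in one arm share a value D away from everyone else, and ignore all other variation, as happens when D becomes very large.

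- Difference in means: mD/n.
- Pooled variance: D² × [m(n − m)/n] / (2n − 2).
- Standard error: √(pooled variance × 2/n).
- D cancels, so t = (m/n) / √{[m(n − m)/n]/(2n − 2) × 2/n}.

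For n = 32 and m = 1: (1/32) / √{[31/32]/62 × 2/32} = 0.03125/0.03125 = 1.00.

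| Girls affected | Limiting t, n = 32 | Limiting t, n = 21 |
|---|---|---|
| 1 | 1.00 | 1.00 |
| 2 | 1.44 | 1.45 |
| 3 | 1.79 | 1.83 |
| 4 | 2.10 | 2.17 |
| Critical value | 2.00 (62 df) | 2.02 (40 df) |

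The extreme girls inflate the variance along with the mean. Up to three therefore cannot make the test significant on their own, however extreme they are. This needs no laboratory SD.

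**With ordinary variation added.** The documents give no laboratory SDs, so shifts of 3, 5, 8 and 10 SD are assumptions. In 100,000 simulated two-sample t-tests per setting, 32 against 32, the proportions with p < 0.05 were:

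| Girls affected | 3 SD | 5 SD | 8 SD | 10 SD |
|---|---|---|---|---|
| 1 | 4.9% | 4.6% | 3.7% | 2.9% |
| 2 | 7.3% | 8.5% | 8.4% | 7.2% |
| 3 | 11.2% | 16.1% | 19.2% | 19.6% |

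A 5 SD shift in one girl moves the arm mean by 5/32 = 0.16 SD, against a standard error of √(2/32) = 0.25 SD.

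**What counts would show.** Exact 95% intervals: 0/32 has an upper limit of 10.9%; 3/32 is 9.4% (2.0 to 25.0%); 4/32 is 12.5% (3.5 to 29.0%). As a between-arm test, counts are weak too: Fisher p = 1.00, 0.49, 0.24, 0.11, 0.053 and 0.024 for 1 to 6 girls against none.

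**Reach of carry-forward.** Section {14} plans for the case that up to one third of participants drop out: 64 − 42 = 22 girls, 11 per arm. That is a ceiling for withdrawal for any reason, not an estimate of laboratory withdrawals.

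**The case against.** The strongest reply is that the sentence on means is a generic closing line in a condensed article. It cannot be an exclusive rule, because adverse events and Tanner stage are also listed outcomes. Worst values, reference-range counts and a treated-patients safety set are ordinary analysis-plan content. Affected girls also have other channels: {11b} stops medication and follows liver and kidney function, and {22} records and codes adverse events.

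Much of this stands. The protocol does not say that only means will be reported, and an unseen analysis plan may add counts. Clinically apparent events and discontinuations are captured separately. Two things remain. The mean rule and the carry-forward rule are written here, with no exemption, so this is a matter of what is stated and not of silence. And {22} collects events by non-systematic questions about the girl's health, which can miss a silent rise in potassium or creatinine that falls short of stopping.

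A reader might infer that an abnormal unscheduled value would be replaced by an earlier one. The text does not support that. Section {20c} fills only missing values, only for withdrawn girls and only if necessary. The earlier visit used could even be the abnormal one or the end-of-study visit, since the protocol does not say which. Nor does the completers analysis discard anything, as it is additional to intention to treat.

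It is also fair that counts do not rescue power at this size, and that a large shift in three girls would be visible to the eye: 3 × 8/32 = 0.75 SD. The t limits show what the test of means cannot do. They do not measure the benefit of counting.

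**Conclusion.** The point holds in a limited form. As written, the between-arm laboratory safety summary is a comparison of means at fixed visits, possibly with carried-forward values. It does not show how many girls met the protocol's own laboratory criteria. Up to three girls in an arm of 32 with a shared extreme value cannot alone make a test of means significant (limiting t 1.00, 1.44, 1.79 against 2.00).

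This uses a two-sample t-test in place of the adjusted repeated-measures ANOVA, for which the protocol gives no model detail. The simulated rejection rates also rest on assumed SD shifts.

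It would go too far to conclude that girls are unprotected, that harms go unrecorded or that the primary result is affected; the documents support none of these. The change is worth making because safety is a stated objective and the remedy uses data already collected.

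**What to change.** In Assessment of outcomes and in {20c}, add one sentence each: laboratory safety markers, and glucose as a stopping criterion, are exempt from carry-forward and are analysed as observed in all girls who took study medication, including unscheduled and end-of-study samples.

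Report by arm the number of girls outside the laboratory's reference range and the number meeting each {11b} laboratory criterion, with exact 95% confidence intervals. Where a criterion has no numeric limit, as with a progressive rise, define it beforehand or count the girls stopped for it. Read these figures descriptively and keep the visit means as a supplement.

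The cost is two sentences and one extra table, with no new visits or samples. The gain is that affected girls become visible by arm; power does not increase.
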